## Trial design {8}

The STATAMED study will be conducted as a prospective, cluster-randomised controlled trial (C-RCT) using a stepped-wedge design at six hospital sites. The catchment areas of the participating sites will be divided into clusters based on postal codes. Clusters were formed using the number of referring entities (e.g. GPs, specialists, nursing homes, ambulatory care services, and emergency services) as the criterion, with the goal of creating a sufficient number of clusters of approximately equal size to facilitate analysis and ensure sufficient statistical power [34].

The stepped-wedge design entails each cluster beginning in a control phase and sequentially transitioning to the intervention phase in staggered steps. Each cluster undergoes a 3-month transition phase to practice and refine the intervention before fully entering the intervention phase. The shift from the control phase to the transition phase is divided into four steps, with one-quarter of the clusters transitioning every 3 months. This staggered approach allows intervention effects to be recorded and compared over time [35]. Once a cluster transitions into the intervention phase, it will remain in this phase for the duration of the study. After the intervention phase, a follow-up phase will be conducted to complete all outcome measurements. Figure 1 illustrates the study design.

**Fig. 1 Fig1:**
[figure not shown]
Study design

The intervention group consists of all eligible patients (see the “Eligibility criteria {10}”) treated in the STATAMED wards. Eligible individuals must be covered by one of the participating statutory health insurers and meet the eligibility criteria. Claims data will only be provided for individuals insured by one of the participating statutory health insurers.

Additionally, three control groups are planned:Control group 1 consists of patients who meet the eligibility criteria for treatment in a STATAMED ward but receive usual hospital care at a non-STATAMED hospital because their referring entity is located in a cluster assigned to the control phase at the time of treatment. This is the standard control group in the stepped-wedge design, enabling the analysis of each cluster before and after STATAMED is introduced.Control group 2 consists of patients who meet the eligibility criteria for treatment at a STATAMED ward and whose referring entity is located in a cluster assigned to the intervention phase at the time of treatment but who are referred to and receive treatment at a non-STATAMED hospital. This group allows for the examination of possible selection effects (i.e. patients who prefer usual hospital care over STATAMED).Control group 3 consists of patients who meet the eligibility criteria for treatment at a STATAMED ward but whose referring entity is located outside a participating hospital site’s catchment area, resulting in treatment at a non-STATAMED hospital. This group allows for the consideration of additional spatial effects. Figure 2 illustrates the various control groups.

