#### Exclusion criteria for patients

Patients will be excluded if they meet any of the following criteria: They require highly technical diagnostic procedures (as defined by the eligibility criteria for STATAMED wards), require inpatient surgery, or have been transferred from other hospitals.

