### Intervention description {11a}

STATAMED encompasses a range of interventions designed to ensure continuity of care and improve coordination between hospital and outpatient settings both before and after hospital discharge. The following interventions will be implemented:Short-stay ward: Each participating hospital site will include (or, in the case of very small hospitals, consist of) a dedicated short-stay ward (“STATAMED ward”) for patients with general medical conditions who require inpatient treatment, have a diagnosis matching a STATAMED-specific ICD-10 code, and are expected to have an uncomplicated disease course (see eligibility criteria {10}). The average length of stay in a STATAMED ward is anticipated to be approximately 3 days.Case review: To determine whether a patient is suitable for treatment in a STATAMED ward, a mandatory case review will be conducted between the referring physician and the lead STATAMED physician of the respective STATAMED ward. During this review, diagnoses will be assessed and discussed, eligibility will be confirmed, and a treatment plan will be collaboratively developed. If the lead STATAMED physician approves the admission, a planned admission will be scheduled, specifying the date and time to ensure that the STATAMED ward can prepare for the patient’s arrival and admit him or her without delay.Case manager: Case managers in each STATAMED ward will coordinate interdisciplinary and cross-sectoral treatment planning for the post-discharge period. During the hospital stay, they will participate in medical rounds to support discharge planning. Their responsibilities include assisting patients with urgent social care needs, such as arranging home care services, procuring assistive devices, and securing short-term care home placements. After discharge, case managers will help coordinate necessary therapeutic measures, including organising nursing services, scheduling physiotherapy sessions, arranging home visits by occupational therapists, and making appointments with outpatient physicians. They will also communicate with and involve the patient’s caregivers and relatives as needed. Case managers hold a basic qualification in a medical, therapeutic, nursing, or social care profession (e.g. medical assistants) and have received project-specific training to prepare them for their tasks in the STATAMED trial.Mobile nurses: These nurses will provide follow-up care either at the patient’s home or in a long-term care facility. Their responsibilities include medical tasks such as monitoring vital signs, collecting blood samples for analysis, and performing ultrasounds or electrocardiograms. They also assess patients for functional deficits, provide fall prevention guidance, and report on follow-up care needs. Additionally, mobile nurses can assist with the admission process. If a patient’s regular referring physician is unavailable, the mobile nurse can visit the patient before admission to assess their condition. In such cases, the lead STATAMED physician will be consulted via telemedicine to make the admission decision, and the mandatory referral case review will take place at a later date.

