### Participant timeline {13}

The participant timeline consists of three phases:Pre-hospital phase: The timeline starts before the hospital stay with an interaction between a potential participant and a referring entity (e.g. a GP), during which the need for hospitalisation is assessed. If the referring entity determines that the potential participant meets the eligibility criteria for the intervention, the STATAMED ward is contacted for the mandatory case review between the referring physician and the lead STATAMED physician. If the eligibility criteria are met, the admission is scheduled to take place approximately 1–2 days later.Hospital phase: Upon provision of informed consent and admission to the STATAMED ward, participants are formally enrolled in the study. The hospital stay is expected to last approximately 3 days on average. During this period, patients receive standard general medical treatment in the STATAMED unit, and case managers assist with interdisciplinary care planning and discharge preparations.Posthospital phase (up to 28 days after discharge): After discharge, follow-up care is available. The mobile nurse may visit the patient at home or in a care facility. Case managers can assist patients during the hospital stay and after discharge, coordinating follow-up care and addressing post-discharge needs.

Figure 3 illustrates the participant timeline, covering the pre-hospital, hospital, and posthospital phases.

All assessments of primary and secondary outcomes will be conducted using claims data from statutory health insurers. Data collection does not require any direct involvement from participants.

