### Concealment mechanism {16b}

This is not applicable. Patients who meet the eligibility criteria and whose referring entity is located in a cluster assigned to the transition or intervention phase can participate in STATAMED. Before admission to a STATAMED ward, patients must provide informed consent to participate in the project.

The control groups will consist of patients who meet the eligibility criteria but receive treatment at a non-STATAMENT hospital. They will be identified retrospectively based on ICD-10 codes available in the claims data from the participating health insurers.

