### Methods in analysis to handle protocol nonadherence and any statistical methods to handle missing data {20c}

At the patient level, nonadherence is expected to be minimal because no specific procedures are strictly required of patients once they have decided to participate in STATAMED. Furthermore, claims data are collected by the participating statutory health insurers independently of the progress of the study, making data delivery and quality independent of patient behaviour.

However, nonadherence may occur due to differences in how the various intervention components are implemented in the STATAMED wards. To address this, STATAMED staff members are required to document their tasks, including evidence of the mandatory case review between the referring entity and the lead STATAMED physician before the admission. The mobile nurse and case manager are also required to document their activities. Likewise, STATAMED wards document any request for components of the intervention that could not be carried out (e.g. due to capacity constraints). This information makes it possible to identify and evaluate nonadherence caused by implementation differences at the STATAMED wards.

Nonadherence can also occur at the level of the referring entity, particularly if patients are referred who do not meet the eligibility criteria. Although a mandatory case review is conducted before admission, the lead STATAMED physician cannot verify the accuracy of the information provided by the referring entity until the patient is admitted. If patients are wrongly admitted due to incorrect information provided by the referring entity, these patients will be transferred to a non-STATAMED hospital.

A fundamental challenge in preparing the data is missing information. Because administrative billing data are collected from a wide range of stakeholders (e.g. doctors, pharmacists, hospitals, medical supply stores), inconsistencies and missing data inevitably occur—both from errors early in the documentation process (e.g. incorrectly issued prescriptions) and from problems in later phases of data collection. When handling missing data, each case is reviewed to determine whether imputation is appropriate and, if so, which method should be employed.

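### The intervention group is defined by eligibility, which can be overturned after enrolment; read literally, patients found ineligible on the ward fit no group, contrary to the intention-to-treat aim

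*Protocol article*

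**What the plan says.** Five parts of the protocol article bear on this.

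- **Group definition, {8}.** "The intervention group consists of all eligible patients" treated in the STATAMED wards, restricted to members of the participating insurers. All three control groups must also meet the eligibility criteria and be treated at a non-STATAMED hospital.
- **Enrolment, {13}.** "Upon provision of informed consent and admission to the STATAMED ward, participants are formally enrolled in the study".
- **Eligibility check.** Under {11a} it normally precedes admission: "During this review, diagnoses will be assessed and discussed, eligibility will be confirmed, and a treatment plan will be collaboratively developed". {11c} allows the review to follow admission in some situations and has patients who then prove ineligible moved to another ward or hospital. {20c} adds that the lead physician "cannot verify the accuracy of the information provided by the referring entity until the patient is admitted", and continues: "If patients are wrongly admitted due to incorrect information provided by the referring entity, these patients will be transferred to a non-STATAMED hospital". Neither {11c} nor {20c} says how these patients are analysed.
- **Transfers.** The patient exclusion criteria in {10} rule out those who "require inpatient surgery, or have been transferred from other hospitals". {18b} allows the data of patients transferred for worsening or additional diagnostics to stay in the analysis unless consent is withdrawn. {20a} plans intention-to-treat and per-protocol analyses so that transfers during STATAMED treatment do not cause bias.
- **Controls, {16b}.** "They will be identified retrospectively based on ICD-10 codes available in the claims data from the participating health insurers".

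**The concern.** An intention-to-treat population is fixed by something known at or before entry. Here entry is consent and admission, but membership of the intervention group depends on a property that ward staff may revise later. If {8} is applied as worded, patients admitted on wrong referral information are removed after enrolment, and only on the STATAMED side.

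Two things are at stake. First, such patients may well be more complex than the rest. If so, losing them would make readmissions look rarer and, once onward days are counted, hospital stays look shorter. Second, a referral that turns out to be wrong is one way the STATAMED pathway can fail, and a pragmatic evaluation should count it.

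The boundary is also a matter of judgement. Needing highly technical diagnostics is an exclusion criterion in {10}, while needing diagnostics beyond the ward's capability is a reason for transfer in {11b}, with data retained under {18b}. The same patient could be recorded either way by staff who are not blinded.

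**Working it through.** The plan states no figure on this point, so there is nothing to reproduce. The check has two parts.

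**1. Follow one patient through the definitions.** Take an insured patient who consents, is admitted, is then found not to meet the criteria and is moved to a non-STATAMED hospital.

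- {13}: enrolled.
- {8}, intervention group: not a member, because not eligible.
- {8}, control groups 1 to 3: not a member, because each requires eligibility. The onward stay is also a transfer from another hospital, which {10} excludes. A patient moved to another ward of the same hospital ({11c}) fails as well, because controls are treated at non-STATAMED hospitals.
- {18b}: not named; the retention rule covers worsening and additional diagnostics.
- {20a}: possibly covered, because the intention-to-treat sentence speaks of transfers without giving reasons.

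So {8} and {10} place the patient in no group, while {20a} can be read as keeping the patient in. The two readings give different analysis populations. A usual-care patient with a qualifying ICD-10 code meets no described check after admission that could remove them in the same way.

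**2. Illustrate the size.** Let q be the share of enrolled patients later found ineligible, and r their mean outcome relative to the other enrolled patients. Neither is in the documents; both are assumptions.

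- Mean over all enrolled, relative to the mean over those kept: 1 + q(r − 1).
- Apparent relative reduction with no true effect, if all such patients leave the intervention group and all their counterparts stay among the controls: 1 − 1/(1 + q(r − 1)).

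| q | r = 1.5 | r = 2 |
|---|---|---|
| 3% | 1 − 1/1.015 = 1.5% | 1 − 1/1.03 = 2.9% |
| 5% | 1 − 1/1.025 = 2.4% | 1 − 1/1.05 = 4.8% |
| 10% | 1 − 1/1.05 = 4.8% | 1 − 1/1.10 = 9.1% |

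The yardstick is the effect in Sample size {14}: 15% initially, 20% after the update. The largest cell is 9.1/15 = 61% or 9.1/20 = 46% of that effect; the smallest is 1.5/15 = 10% or 1.5/20 = 8%.

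**Direction.** Outcomes {12} measures length of stay from admission to discharge date. If only the days on the STATAMED ward count, a wrongly admitted patient who is moved on quickly has a short stay. Then r is below 1, the expression turns negative, and dropping such patients makes STATAMED stays look longer. For length of stay, the table applies only if onward days are attributed to the patient.

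**The case against.** The strongest reply is that a reader might infer that the protocol drops these patients from the analysis, and it nowhere says so. That inference comes from joining the definition in {8} to the exclusion in {10}. The intention-to-treat sentence in {20a} does not separate transfers by reason and could cover the wrongly admitted. {18b} keeps those transferred for worsening or more diagnostics, which may be most of the complex cases. {10} asks for an expected uncomplicated course, so a patient who merely turns out sicker does not thereby become ineligible. This stands: the concern is confined to patients found ineligible, and the exclusion is permitted rather than stated.

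A reader might also infer that eligibility can be checked only after admission. The documents do not support that either: the case review normally confirms it beforehand, and what cannot be verified earlier is the accuracy of the referral information.

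Nor is it established that all usual-care counterparts stay in. {8} requires controls to meet the criteria, and claims hold diagnoses and procedures that could screen some of them out. What stands on our side is that no filter equivalent to the ward's check is described.

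Keeping the onward stay from entering as a new control admission is sensible, since it avoids double counting. The gap is that the stay is not assigned to the intervention patient instead.

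Finally, analysis-set detail is often left to the analysis plan. But the group definition, the enrolment point and the intention-to-treat aim all stand in this article, and they do not agree.

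**Conclusion.** The point holds as an inconsistency between stated rules. {8} defines the intervention group by eligibility and treatment received, {13} enrols before eligibility is beyond revision, {11c} and {20c} foresee the revision without giving an analysis rule, and {20a} promises intention-to-treat. Applied literally, {8} allows a post-enrolment exclusion in one arm.

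It is not shown that the exclusion will occur, how large it would be, or, for length of stay, which way it would act. The range of about 1.5–9% rests wholly on assumed shares of 3–10%, assumed outcome ratios of 1.5–2, complete removal in one arm and none in the other, and, for length of stay, attribution of onward days. The bias is small if few patients are affected. It matters against the planning effect near 10% with clearly worse outcomes. The documents do not support treating the upper figure as the expected bias.

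**What to change.** In {8}, define the intervention group for the intention-to-treat analysis as all insured patients enrolled under {13}, whatever is later found about their eligibility, and attribute the onward hospital stay to them. Apply any eligibility filter only through claims variables that are used identically in the intervention and control groups. Then reconcile {8}, the exclusion criteria in {10}, {11c}, {13}, {18b}, {20a} and {20c}, so that each gives the same analysis status to a patient found ineligible after admission. This concerns analysis membership only and leaves the clinical handling of transfers untouched.

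The cost is wording in the protocol and the analysis plan. Claims for insured patients are collected independently of the trial, so no new data collection is needed. It is best settled before the final data delivery, expected around January 2027 ({18a}). The downside is that the estimated benefit may be slightly smaller.

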The current trial evaluates a new model of care, referred to as STATAMED, which aims to address the challenges outlined above. At participating hospitals, a general medicine short-stay ward (“STATAMED ward”) with approximately 20 beds will be integrated into the existing hospital infrastructure. Two implementation models can be distinguished: (1) Hospitals in which a STATAMED ward is established and operates alongside existing wards and (2) hospitals in which the STATAMED ward constitutes the sole inpatient ward. In addition to standard general medical treatment, STATAMED wards will include interdisciplinary treatment planning before hospital admission (facilitated through a mandatory case review between the referring physician and the lead STATAMED physician), as well as support from case managers and mobile nurses during and after the hospital stay to ensure coordination and continuity of care after hospital discharge.

The mandatory case review between the referring outpatient physician and the lead STATAMED physician is conducted to determine patient eligibility for the trial and to collaboratively plan the treatment. While the literature supports the benefits of better-integrated models of service delivery [18], mandatory case reviews between referring physicians and lead physicians at receiving hospitals are currently neither widely implemented nor thoroughly studied.

Short-stay units are employed in various medical contexts, including paediatric care, surgical care, emergency care, and general medicine. Depending on the setting, the intended length of stay in short-stay units is typically 5 days or fewer [19]. In a meta-analysis, Damiani et al. [19] found that short-stay units reduced length of stay without adversely affecting mortality and readmission rates. However, a literature review by Strøm et al. [20] focusing on general medical conditions concluded that current evidence regarding reduced mortality, serious adverse events, and rehospitalisation is insufficient to definitively assess the benefits and harms of short-stay units.

The primary motivation for deploying case managers is to improve care coordination, which involves communication with various health care providers, social service providers, and the patients’ relatives. A literature review by Joo et al. [21] found that case managers reduce readmissions, hospital visits, emergency department visits, and length of stay.

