### Eligibility criteria {10}

#### Inclusion criteria for patients

Patients are eligible for inclusion if they meet the following criteria: They present at a participating referring entity with a general medical condition requiring inpatient treatment as defined by the German Appropriate Evaluation Protocol (G-AEP), have a diagnosis corresponding to an ICD-10 code designated specifically for this project (i.e. conditions relevant to the trial), and are expected to have an uncomplicated course of disease corresponding to a patient clinical complexity level (PCCL) of 0 to 2. Additionally, patients must be at least 18 years of age.

The following list of ICD-10-GM (2023) codes includes exemplary diagnoses relevant to the study but is not exhaustive:I10.01 (benign essential hypertension: with mention of hypertensive urgency)I48.1 (persistent atrial fibrillation)E86 (volume depletion)K59.09 (other and unspecified constipation)I50.14 (left ventricular failure: with symptoms at rest)I20.8 (other forms of angina pectoris)I48.0 (paroxysmal atrial fibrillation) and R55 (syncope and collapse)R07.3 (other chest pain) and K29.6 (other gastritis)N39.0 (urinary tract infection, site not specified)I50.13 (left ventricular failure: with symptoms under mild strain)J20.9 (acute bronchitis, unspecified)J18.9 (pneumonia, unspecified)I50.01 (secondary congestive heart failure)K57.32 (diverticulitis of large intestine without perforation, abscess, or bleeding)E11.91 (type 2 diabetes mellitus: without complications, uncontrolled)R10.3 (pain localised to other parts of lower abdomen)A09.9 (gastroenteritis and colitis of unspecified origin)K29.1 (other acute gastritis)

The complete list of ICD-10 codes can be provided upon request.

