### Implementation {16c}

The allocation sequence will be generated through randomisation (see “Sequence generation {16a}”). The randomisation process will be conducted by the authors.

Participants will be enrolled at their respective STATAMED wards. Assignment to the intervention will depend on the cluster to which the referring entity is assigned. Patients who meet the eligibility criteria and whose referring entity is in a cluster currently in the intervention phase will be able to participate in STATAMED.

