### Statistical methods

#### Statistical methods for primary and secondary outcomes {20a}

The two co-primary outcomes (length of hospital stay, 30-day hospital readmission rate) are treated as continuous variables. The secondary outcomes (utilisation of hospital emergency departments, emergency outpatient care, and nonemergency outpatient care, as well as place of discharge) are also continuous except for the place of discharge (home, care facility, other), which is categorial.

Because there are two co-primary outcomes without hierarchical ordering, a correction for multiple testing is required. A Bonferroni correction will be applied, resulting in a one-sided significance level of α/2 = 2.5% for each primary outcome given a global type I error rate of *α* = 5%. However, the Bonferroni method is known to be conservative. As an alternative, the Romano-Wolf procedure [43] may be used, as it more efficiently controls the family-wise error rate by accounting for the dependence structure among outcomes through resampling (see “Sample size {14}”).

When analysing stepped-wedge designs, it is important to account for temporal effects given that each cluster transitions to the intervention in a stepwise fashion. In this study, this is particularly important because the STATAMED wards will gain experience with implementing the intervention over time. Additionally, the longitudinal design of the study necessitates the consideration of calendar time because patient case mix may vary by season (e.g. winter versus summer) due to the focus of the study on general medical conditions. To account for these temporal effects, generalised linear mixed models (GLMMs) and generalised estimating equations (GEEs) will be applied [45–47]. Propensity score matching, considering age, gender, and morbidity, will be used to ensure comparability between the control and intervention groups.

To avoid bias from patients who are transferred to other hospitals during STATAMED treatment or those who meet eligibility criteria but prefer to be treated at a non-STATAMED hospital, the analysis will be conducted according to the intention-to-treat and per-protocol principles [48].

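### The trial groups are defined by place of treatment and screened differently, so intervention group versus control group 1 is an as-treated contrast, and the promised intention-to-treat set is left undefined

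*Protocol article*

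**What the plan says.** **Groups.** In the protocol article, Trial design {8}, the text below Figure 1 opens with "The intervention group consists of all eligible patients" and ties membership to treatment in a STATAMED ward. Control group 1, called the standard stepped-wedge control, is made up of eligible patients who "receive usual hospital care at a non-STATAMED hospital because their referring entity is located in a cluster assigned to the control phase". Control group 2 has a referrer in an intervention-phase cluster but treatment at a non-STATAMED hospital; its stated use is to look at selection. Control group 3 lies outside the catchment areas. Study setting {9} repeats that control data come from non-STATAMED hospitals. Background and rationale {6a} gives as one implementation model: "Hospitals in which a STATAMED ward is established and operates alongside existing wards".

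**Screens.** Inclusion criteria ask for patients who "are expected to have an uncomplicated course of disease corresponding to a patient clinical complexity level (PCCL) of 0 to 2". Intervention description {11a} has a mandatory case review decide suitability, and section {26a} requires consent at admission. For controls, Concealment mechanism {16b} says: "They will be identified retrospectively based on ICD-10 codes available in the claims data from the participating health insurers". They give no consent.

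**Analysis.** Statistical methods {20a} promises intention-to-treat and per-protocol analyses (the Abstract says intention-to-treat and actual treatment). On comparability it says: "Propensity score matching, considering age, gender, and morbidity, will be used to ensure comparability between the control and intervention groups".

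**Transition phase.** Section {16b} admits eligible patients "whose referring entity is located in a cluster assigned to the transition or intervention phase can participate in STATAMED", whereas Implementation {16c} names those "whose referring entity is in a cluster currently in the intervention phase will be able to participate in STATAMED".

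**The concern.** What is randomised is the time at which a cluster crosses over. That protects one comparison: all eligible admissions in intervention-phase cluster-periods against all eligible admissions in control-phase cluster-periods. The groups described here depart from it in two ways. Membership depends on where the patient was treated, which is decided after randomisation. It also depends on a screen that differs between the arms.

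Both co-primary outcomes, length of stay and 30-day readmission, depend on how complicated the illness is. If one side is filtered by a physician's view that the course will be uncomplicated and the other by diagnosis codes, the two sides can differ with no effect of STATAMED at all. The result is meant to support a recommendation on adopting the model in routine care, so this matters beyond wording.

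**Working it through.** The article gives no figure on this point to reproduce. The check sets its definitions side by side and then shows two illustrations.

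**1. Who is in which group (catchment-area patients)**

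| Place of treatment | Cluster in control phase | Cluster in intervention phase |
|---|---|---|
| STATAMED ward | not expected | intervention group |
| Ordinary ward of a STATAMED hospital | no group | no group |
| Non-STATAMED hospital | control group 1 | control group 2 |

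Intention-to-treat compares the two columns. Intervention group versus control group 1 compares one cell from each. Pooling the intervention group with control group 2 comes closer, but still omits the middle row, and that row does not stay constant. Strategies to improve adherence {11c} foresees moves from other wards of the same hospital into the STATAMED ward. After crossover, some middle-row patients therefore become intervention patients, while their control-phase counterparts are counted nowhere.

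**2. How patients are screened**

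| Element | Intervention group | Control groups |
|---|---|---|
| Diagnosis | listed ICD-10 code | listed ICD-10 code |
| Prognosis | judged in advance at case review | nominally the same criterion; no stated way to apply that judgement |
| Participating referrer | required | not visible from ICD-10 codes alone |
| Consent | required | not required |
| Removal on withdrawal of consent ({18b}) | possible | not possible |

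Matching uses age, gender and morbidity. It may recover part of the prognostic judgement, but it cannot be assumed to recover all of it.

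**3. Possible size under no true effect (unadjusted illustration)**

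Assumed, not in the article: f, the share of code-screened controls whom the review would have refused, and r, their mean stay relative to the others. The control mean is (1 − f) + f·r = 1 + f(r − 1) times the intervention mean, so

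apparent reduction = 1 − 1/(1 + f(r − 1)).

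| f | r = 1.5 | r = 2.0 |
|---|---|---|
| 0.1 | 1 − 1/1.05 = 4.8% | 1 − 1/1.10 = 9.1% |
| 0.2 | 1 − 1/1.10 = 9.1% | 1 − 1/1.20 = 16.7% |
| 0.3 | 1 − 1/1.15 = 13.0% | 1 − 1/1.30 = 23.1% |

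Sample size {14} initially sets 15% as the relevant difference. An apparent 15% needs f = (1/0.85 − 1)/(r − 1), which is 0.35 at r = 1.5 and 0.18 at r = 2.0. No allowance is made for matching, so this shows what could happen and is not an estimate.

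**4. What an intention-to-treat set does to the effect**

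From Sample size {14}: revised effect 20%, revised requirement 2076. Assumed: uptake u among eligible patients in intervention-phase clusters, and no effect in those treated elsewhere. The effect becomes 20% × u, and by simple inverse-square scaling the requirement becomes 2076/u².

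| u | Effect | Scaled requirement |
|---|---|---|
| 0.90 | 18% | 2563 |
| 0.75 | 15% | 3691 |
| 0.50 | 10% | 8304 |

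If the 2076 are ward patients and control group 2 comes on top, the set at u = 0.75 holds 2076/0.75 = 2768, still short of 3691. The scaling holds everything else fixed; power and the baseline readmission rate are not given, so an exact recalculation is not possible.

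**The case against.** The strongest reply is that the pieces of an intention-to-treat analysis are already there. Control group 2 keeps eligible patients from intervention-phase clusters who went elsewhere. Table 1 in section {18a} collects referrer identifiers and postal codes so that claims can be assigned to clusters. Section {18b} keeps the data of patients transferred out, and {20a} names the very selection problem that intention-to-treat should solve. This stands. A reader might infer that an intention-to-treat comparison cannot be formed; the article does not support that. It leaves the set undefined and omits one part of it.

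Secondly, controls are said to meet the eligibility criteria, and claims hold procedures and diagnoses, so they are not unselected. That is fair. What is missing is any stated means of applying a prospective prognostic judgement to them.

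Thirdly, a reader might conclude that the bias is shown to favour STATAMED, or might size the ordinary-ward gap from bed numbers at the largest site. Neither follows. The article reports no refusal rate and no stay for refused patients. Beds are not eligible admissions, and where the STATAMED ward is the sole inpatient ward the gap does not arise.

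Fourthly, the transition-phase wording may be settled by Figures 1 and 2, which could not be seen, and {16c} does not say that only intervention-phase patients take part. Which analysis is primary may properly be left to the analysis plan. Neither point carries the finding.

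**Conclusion.** The point holds in limited form. Followed as written, the definitions give an as-treated contrast between groups screened differently, with eligible patients on ordinary wards of STATAMED hospitals in no group and control group 2 on the control side. Randomisation does not protect that contrast, and the planned matching cannot be assumed to restore comparability. This goes beyond detail left to an analysis plan, because the group definitions themselves are fixed in the article.

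The likely direction is in favour of STATAMED, since the review selects patients expected to do well, but this is reasoning and has not been demonstrated. The 9% to 17% range depends wholly on an assumed 20% refusal share and an assumed stay ratio of 1.5 to 2, before any matching. In an analysis by cluster phase, non-uptake would instead pull the estimate towards no effect.

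**What to change.** - **Define the intention-to-treat set.** Take all admissions of participating-insurer members that meet one claims-based screen: listed ICD-10 codes, age, no transfer from another hospital, and the same procedure and complexity filter. Apply it identically in every cluster-period and classify each admission by the phase of the referrer's cluster on the admission date. Compare the intervention group plus control group 2 with control group 1.
- **Close the gap.** In control groups 1 and 2, replace treatment at a non-STATAMED hospital with treatment anywhere other than a STATAMED ward, and bring Study setting {9} into line.
- **Keep the matched as-treated contrast** as a supporting analysis, labelled as such.
- **Reconcile** Trial design {8}, {16b} and {16c} on whether transition-phase patients are participants and whether they are analysed.
- **Keep the exclusion of patients who withdraw consent** ({18b}), but report their number, since it can affect one side only.
- **Restate the effect that 2076 participants can detect** in this analysis over a range of uptake, as in the last table above.

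The cost is protocol and analysis-plan wording and a wider extract from claims that the insurers already hold. The final delivery is expected around January 2027, so the screen can be fixed beforehand. The real price is dilution: at an assumed 75% uptake the 20% effect becomes 15%, and the trial may be less able to detect it than the present calculation implies.
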